# Community Health workers United to Reduce Colorectal cancer and cardiovascular disease among people at Higher risk (CHURCH): study protocol for a randomized controlled trial

**DOI:** 10.21203/rs.3.rs-3797889/v1

**Published:** 2024-04-09

**Keywords:** colorectal cancer, community-based research, health disparities, randomized trial, community health workers, inflammation, dietary pattern

## Abstract

**Background::**

Colorectal cancer (CRC) is the second most lethal cancer in the United States (U.S.) with the highest incidence and mortality rates among African Americans (AAs) compared to other racial groups. Despite these disparities, AAs are the least likely to undergo CRC screening, have precancerous colorectal polys removed, and have CRC detected at stages early enough for curative excision. In addition, compelling evidence links inflammatory dietary patterns to increased CRC and cardiovascular disease risk. Studies show that AA churches can successfully engage in health promotion activities including those related to cancer control. The current study seeks to leverage church-placed Community Health Workers (CHWs) to increase CRC screening and reduce CRC risk.

**Design and Methods::**

We aim to (1) increase guideline concordant CRC screening uptake using church-placed CHWs trained in screening with a validated instrument, Brief Intervention using Motivational Interviewing, and Referral to Treatment (SBIRT); and (2) reduce dietary risk factors (inflammatory dietary patterns) linked to CRC. The latter will be addressed by culturally adapting an existing, web-based lifestyle program called Alive!. Using a Hybrid Type 1 Implementation-Effectiveness cluster randomized design, we will randomize 22 AA churches into either the dual intervention arm (CHW-led SBIRT intervention plus Alive!) or a usual care arm comprised of CRC prevention educational pamphlets and a list of CRC screening sites. We will recruit 440 subjects and evaluate the effects of both arms on screening uptake (colonoscopy, fecal DNA) (primary outcome) and dietary inflammation score (secondary outcome) at 6-months follow up, and Life Simple7 (LS7) - a cardiovascular disease (CVD) risk score - at 6 months and 1-year (secondary outcome). Finally, guided by a racism-conscious adaptation of the Consolidated Framework for Implementation Research (CFIR), we will conduct a mixed-methods process evaluation with key stakeholders to understand multi-level influences on CRC screening and CVD risk behaviors.

**Discussion::**

Church-placed CHWs are trusted influential connectors between communities and health systems. Studies have shown that these CHWs can successfully implement health prevention protocols in churches, including those related to cancer control, making them potentially important community mediators of CRC screening uptake and CRC/CVD risk reduction.

**Trial registration::**

NCT05174286

## Introduction

### Background and Rationale {6a}

African American (AA) adults are more likely to contract and die from colorectal cancer (CRC) than any other racial group in the United States (U.S). Despite data showing that screening colonoscopies are associated with strong reductions in CRC incidence and mortality,^1, 2^ AA are the least likely to be screened,^3^ or adhere to risk reducing programs for CRC. There is a dearth of sustainable multi-level interventions targeting AAs that include a dual focus on reducing the burden of CRC and its cardiovascular disease (CVD) risk factors - two devastating diseases with a common social context and similar health disparity profiles. Given the influence and reach of churches and the mediating role of community health workers (CHWs) between churches, communities, and health systems, we propose to test a cluster randomized church-placed intervention, at the center of which are CHW-congregant dyads, to increase guideline concordant CRC screening and decrease related lifestyle risk factors, while understanding contextual factors influencing our outcomes of interest.

#### Burden of Colorectal Cancer Among African Americans

CRC is the second most common cause of cancer deaths in the U.S and a contributor to premature mortality.^4^ AAs have the highest incidence and mortality from CRC and the highest likelihood of being diagnosed at an earlier age and with more advanced disease^5^ compared to other race-ethnic groups.^5^ In fact, late-stage CRC, accounts for more than 60% of the disparity in mortality.^6^ The unexpected death of Chadwick Boseman - lead actor of the Marvel movie “Black Panther”- at the age of 43 years from CRC highlighted these statistics, exposing a lack of awareness about the disease.

According to the New York City Department of Health Mental Hygiene Bureau of Vital Statistics, neighborhood has a dramatic effect on CRC incidence rates, with a 30% higher age-adjusted incidence rate among blacks living in the poorest neighborhoods. Indeed, racial residential segregation has been shown to impact CRC outcomes, and AA patients living in more segregated counties are more likely to present with advanced disease, have lower likelihood of surgical resection, and have worse cancer-specific survival.^7^

#### Racial Disparities in Colorectal Cancer Screening

The disparities discussed in the previous section are not related to genetic differences, but to structural inequities in access to CRC screening, utilization of CRC screening, and quality of CRC treatment.^8, 9^ In fact, the lower screening rates by any method among AAs compared to Whites is the major modifiable driver of CRC disparities.^10^ Moreover, these lower screening rates persist in equal access settings and among insured subjects, making barriers related to healthcare mistrust, health literacy, and perceived risk important to address. For example, although 25% of patients with CRC have a family history, AAs are less likely to know their paternal history or disclose findings of colon polyps to their relatives compared to Whites,^11^ contributing to inequity in screening.

#### Strategies to Improve Colorectal Cancer Screening Uptake Among African Americans

Physician recommendations, physician directed multimodal education with reminders, increased health insurance coverage, the use of patient navigators, and tailored patient education have shown modest benefits on CRC screening uptake.^12^ Notwithstanding, there is a scarcity of rigorously tested approaches leveraging multiple socio-ecological levels of influence (individual, relationship, institutional, community, societal) at the same time, which increases the likelihood of a greater and more sustained impact^13^ and broadens the lens through which the intervention can anticipate pitfalls. For example, one intervention which focused on the institutional level by targeting greater availability of colonoscopists inadvertently increased colonoscopy rates among Whites and decreased rates among AAs.^14^ Other studies suggest that offering stool-based tests such as the Fecal Immunochemical Test (FIT) may improve screening rates^15^ suggesting that a greater emphasis on shared decision-making regarding guideline screening options is beneficial. For individuals aged 45–75 years, these options include: (1) high-sensitivity guaiac fecal occult blood test (gFOBT) or FIT every year; (2) stool DNA test (sDNA)-FIT every 1 to 3 years; (3) computed tomography (CT) colonography every 5 years; (4) flexible sigmoidoscopy every 5 years; (5) flexible sigmoidoscopy every 10 years + FIT every year; (6) colonoscopy screening every 10 years.

### Objectives {7}

The overarching goal of this proposal is to create a scalable community-academic partnership model for CRC and CVD prevention for AA communities. Our dual intervention approach allows us to target two major killers of AAs. We aim to (1) increase guideline concordant CRC screening uptake using a CHW-led Screening, Brief Intervention, and Referral to Treatment (SBIRT) intervention (primary outcome); and (2) reduce dietary and CVD risk factors linked to CRC (secondary outcomes). The latter will be addressed by culturally adapting an existing, evidence-based, web-based lifestyle program called Alive!, which has been shown in several RCTs to improve CVD outcomes. Using a Hybrid Type 1 Implementation-Effectiveness design, we will randomize 22 AA churches (440 subjects) into a cluster RCT to accomplish the following:

#### Aim 1: To compare the effect of SBIRT (Intervention) to Referral As Usual (RAU) (Usual Care) on guideline-concordant CRC screening uptake.

We hypothesize that the intervention will lead to increased CRC screening uptake (colonoscopy, fecal DNA) (primary outcome) compared to RAU at 6-months.

#### Aim 2: To evaluate the effect of a Culturally-adapted Alive! Program (CAP) incorporated into the intervention arm on dietary inflammation score (DIS).

Participants in the intervention group will participate in CAP following the completion of the SBIRT intervention. We hypothesize that participants in the CAP arm will have lower DIS scores compared to RAU at 6-months.

#### Aim 3: To evaluate the effect of CAP on changes in Life Simple-7 (LS7) scores.

We hypothesize that participants in the CAP arm will have improvement in LS7 scores compared to RAU at 6-months and 1 year.

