### Trial Design {8}

We will use a hybrid type 1 effectiveness-implementation design^18^ and a community based participatory research approach (CBPR)^19^ to engage AA churches and study participants. We will conduct a two-arm, cluster RCT in 22 AA churches comparing the effectiveness of CHW-delivered SBIRT (n=11 churches) to RAU (n=11 churches) on CRC screening uptake (colonoscopy, stool-based test) (primary outcome) (Figure 1). We will also examine the effect of an evidence-based CAP program incorporated into the intervention arm on DIS and on changes to CVD risk captured by LS7 scores (secondary outcomes). Lastly, we will utilize a concurrent, mixed-methods approach to assess cultural and contextual factors including barriers and facilitators of screening uptake and implementation in churches. The CFIR^30^ will guide our implementation and process evaluation. We will utilize an adapted version of CFIR, which incorporates a race-conscious lens^16,20^ to generate semi-structured interviews with key stakeholders.

There are 3 waves of data collection: baseline, 6 months, and 12 months; for the CAP there will be an additional 3-month baseline collection of the FFQ.

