## Interventions

### Explanation for the choice of comparators {6b}

This study will compare the effect of SBIRT and CAP (Intervention) to RAU (Usual Care) on guideline-concordant CRC screening uptake. SBIRT is an evidence-based approach, originally designed for people at risk of developing mental disorders,^21^ comprised of three components: (1) Screening with a validated instrument, (2) Brief Intervention, (3) Referral to Treatment. Alive! is an automated platform that includes step-by-step individualized tailoring, feedback, and weekly guidance through interactive emails focused on increasing physical activity, and improving eating patterns. In contrast, the RAU group will receive the most common form of referral from church-based screening events, which includes educational brochures, community resources, and a list of CRC screening sites.

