### Intervention Description {11a}

#### Screening, Brief Intervention, and Referral to Treatment

Multiple studies have found SBIRT to be effective in increasing referral rates for mental health related treatment, and adherence to follow-up.^22–24^ Given the multi-generation trauma related to self-reported discrimination and resulting distrust of the medical system among AA populations,^25^ we decided to adapt SBIRT for CRC screening because it embraces Trauma-Informed Care (TIC).

The screening component will include items that will be adapted from the Behavioral Risk Factor and Surveillance System CRC screening tool to screen guideline adherence at baseline and 6-months.

The brief intervention component of SBIRT will be Motivational Interviewing (MI), which has been shown to be effective at improving health outcomes among AAs in church-based settings when delivered by paraprofessionals.^26^ MI is an empirically tested, person-centered, behavior change intervention designed to guide, elicit, and strengthen motivation for change.^27^ It decreases ambivalence and increases motivation for treatment. Studies of MI have found (1) an increase in CRC screening; (2) an increase in healthy eating patterns; and (3) improved CVD risk factor control among AA adults.^28–30^

CHWs will provide up to six-MI sessions over a three-month period. The exact number of sessions will vary based on participant needs. The sessions will occur in person or virtually via phone/zoom. Data will be collected on method of delivery. MI sessions will help eligible participants move through the various stages of change associated with seeking screening for CRC. In these sessions, CHWs will establish rapport through Open-ended questions, Affirmations, Reflections, and Summary statements (OARS), review reasons for non-compliance with guideline screening, and assess motivation and confidence regarding obtaining a screening test and elicit cognitive, emotional, and socio-economic-related barriers and facilitators of screening. CHWs will also work with participants to consider the ‘pros’ and ‘cons’ of screening, provide screening options for the participant based on the nature of barriers elicited from them and addressing social determinants of health (SDoH)-related needs, assess participant’s values and goals and help them link their current predisposition to screening to their goals, and summarize what was discussed in order to clarify an action plan.

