## Assignment of Interventions: Allocation

### Sequence Generation {16a}

In this study, randomization will occur on the church level to reduce chances of contamination through interactions between congregants in the same church. Four churches will be randomized in Years 1; six churches in Years 2; six churches in year 3; and six churches in year 4 to reach our target sample size of 22 churches. Churches will be matched based on size (number of members) and randomized in a 1:1 ratio to either SBIRT and ALIVE! or RAU. A randomization sequence will be generated by the study statistician according to CONSORT guidelines. Randomization will occur on the church level prior to the start of screening events to allow for assignment to specific booster trainings with the CHWs. At the end of data collection, churches assigned to the RAU arm will be offered SBIRT.

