Regarding the CRC screening rate, a sample size of 198 subjects per group (10 to 12 churches per group, average of 20 subjects per church, attrition rate of 10% at 6 months) is required to provide 80% or greater power to detect a group difference of 15% (a clinically meaningful increase) in the rates of completed colorectal cancer screening at 6 months. Thus, power will be sufficient to detect the hypothesized difference from baseline in both arms. As shown above, these calculations assume a baseline rate of 0 and scenarios with increase in screening rates in the usual care group from 0.20 to 0.50. Thus, with an overall sample size of 440 subjects or 220 per arm (11 churches per arm with 20 subjects in each church), the study is powered adequately, even with attrition. Based on our prior study in which approximately 50% of AAs above age 50 years were not up to date with screening,^48^ we will screen at least 40 adult churchgoers aged 45 years and older per church for study eligibility (total screening = 880 subjects).

#### Power analysis for Aims 2 and 3

Aim 2 is to evaluate the effect of a CAP incorporated into the intervention arm on DIS at baseline and 6-month follow up; and Aim 3 is to evaluate the effect of CAP on changes in LS7 at baseline, 6-months and 12 months. Sensitivity analyses will be performed including data from the 3-month wave. Power calculations were performed for an analysis of covariance (ANCOVA)-type model: *y*_*ijk*_ = *μ*_*jk*_ + *y*_*i*0_ + *τ*_*c*_ + *e*_*ijk*_, where *μ*_*jk*_ is the group mean for follow up DIS and LS7, *y*_*i*0_ is the baseline measure, j=1,2 follow-ups and k=0, 1 for group, *τ*_*c*_ is a random effect for clustering within church. The power analysis equation for one follow-up is: $n=\frac{2{\left(z_{\alpha }+z_{\beta }\right)}^{2}\sigma^{2}\left(1-\rho^{2}\right)g}{d^{2}R_{el}}$: where *ρ* is the correlation between the outcome and baseline values, *σ* is the standard deviation, *d*_*I*_ is the follow-up difference between 2 groups, *R*_*el*_ is the reliability of the outcome, adjusting for clustering within churches, g=1+(s-1)*icc, and n is number of subjects per group.

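### Aims 1–3 credit SBIRT or CAP separately, but the only randomised contrast is SBIRT plus CAP versus usual care; the 3-month FFQ also has two conflicting roles

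*Protocol article*

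**What the plan says.** **What is randomised.** Under Sequence Generation {16a}, churches are "randomized in a 1:1 ratio to either SBIRT and ALIVE! or RAU". The abstract describes a "dual intervention arm (CHW-led SBIRT intervention plus Alive!) or a usual care arm". Under Aim 2, "Participants in the intervention group will participate in CAP following the completion of the SBIRT intervention", and the CAP description confirms that everyone in an intervention church is enrolled in it. Usual care receives brochures, a resource guide and a list of screening sites.

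**What the aims name.** Aim 1 and the Trial Design section present the comparison as SBIRT against referral as usual. The power section for Aim 1 does the same, and its logistic model has one binary term whose value 1 is labelled the SBIRT intervention. Aim 2 names CAP, described as built into the intervention arm. Aim 3 is "To evaluate the effect of CAP on changes in Life Simple-7 (LS7) scores". The hypotheses for Aims 2 and 3 speak of a CAP arm, and the power section for those aims repeats the CAP attribution.

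**What the comparator section names.** "This study will compare the effect of SBIRT and CAP (Intervention) to RAU (Usual Care) on guideline-concordant CRC screening uptake".

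**The 3-month FFQ.** Trial Design {8} counts three waves (baseline, 6 and 12 months) and adds that "for the CAP there will be an additional 3-month baseline collection of the FFQ". The power section for Aims 2 and 3 says "Sensitivity analyses will be performed including data from the 3-month wave". The Outcomes section lists the 3-month FFQ alongside the baseline and 6-month collections.

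**The concern.** One arm-versus-arm difference is labelled an SBIRT effect for one outcome and a CAP effect for two others. The design has no group that receives only one component, so neither label describes what the trial estimates. For the primary outcome the labels also conflict: Aim 1 attributes the screening comparison to SBIRT, while the comparator section attributes it to SBIRT and CAP together.

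At stake is what the trial may conclude. Read literally, a positive DIS or LS7 result would be reported as an effect of the adapted web programme, and a positive screening result as an effect of SBIRT. Neither statement would follow from the comparison made.

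The two descriptions of the 3-month FFQ add a related problem. Whether that measurement is a starting value or a post-randomisation outcome decides how it may enter an analysis, and the protocol points both ways.

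**Working it through.** No sample size, power or alpha figure depends on this point, so there is no stated figure to reproduce. The check is of identifiability and timing.

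1. **Count the contrasts.** Let *s* be the effect of SBIRT over usual care and *c* the further effect of adding CAP after SBIRT, both at 6 months. With two arms, the single estimable quantity is θ = *s* + *c*. SBIRT and CAP assignment both coincide with arm, so there is one equation and two unknowns. The effect of CAP without SBIRT does not appear in the equation at all.

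2. **Illustrate with the plan's own effect size.** The power section gives a detectable DIS difference of 0.303 (Cohen's d), used here only as an example. A true θ of 0.303 is equally compatible with:
   - *s* = 0, *c* = 0.303
   - *s* = 0.15, *c* = 0.303 − 0.15 = 0.153
   - *s* = 0.303, *c* = 0

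   The analysis models contain only an arm term, so they cannot tell these apart.

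3. **Is a non-zero *s* on diet and LS7 plausible?** The SBIRT section lists, among findings of motivational-interviewing studies, "2) an increase in healthy eating patterns; and (3) improved CVD risk factor control among AA adults". That interviewing is SBIRT's brief intervention, and usual care does not receive it. The intervention arm also gets insurance enrolment and help with social needs. On the protocol's own evidence, *s* = 0 cannot be assumed for DIS or LS7.

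4. **Does CAP contact fall before the screening endpoint?** SBIRT runs for as long as three months and CAP then runs 12 weeks, together about six months. CAP coaching is weekly for 4 weeks and then fortnightly for 8 weeks, or 4 + 8/2 = 8 further health-worker contacts. By schedule, these largely precede the 6-month screening assessment. The content is dietary, so an effect on screening may be small, but the 6-month comparison is of arms that differ in both components.

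5. **Place the 3-month FFQ.** It comes after randomisation and, by schedule, at about the end of SBIRT and the start of CAP.
   - *As a baseline covariate:* it conditions on a value SBIRT may already have changed. That can remove part of *s* from the arm difference. What remains is neither the package effect nor a CAP effect protected by randomisation.
   - *As an outcome:* the 3-month arm difference is a legitimate comparison of what had been delivered by then, which is mainly SBIRT.

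   Only the second use is consistent with estimating the package effect.

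**The case against.** The strongest reply is that the package is already stated. The abstract calls the arm dual, Sequence Generation randomises to both components, Aim 2 says CAP sits within the intervention arm, and the Aim 1 hypothesis speaks simply of the intervention. On this view the aim titles are shorthand for the component directed at each outcome. Much of this stands: nothing is concealed, and the arm comparison is a valid intention-to-treat test of the package. The shorthand does not explain why Aim 1 and the comparator section name different interventions for the same outcome, or why Aim 3 states its objective as the effect of CAP.

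A reader might draw stronger conclusions that the protocol does not support:

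- **That adding the 3-month data would dilute or halve the DIS effect.** No averaging of 3 and 6 months is described, and the ANCOVA-type power model has group means specific to each follow-up. Halving would also require no effect at 3 months, which sits badly with the cited benefits of motivational interviewing.
- **That the planned scale-up would be misdirected.** The dissemination section carries SBIRT and Alive! forward together, which is what this trial can inform.
- **That screening tests completed before CAP would isolate SBIRT.** The measures table lists verification of completion at 6 months, without showing that test dates are captured. CAP start also varies between participants and has no counterpart in usual care.
- **That nobody has begun CAP by month 3.** The number of SBIRT sessions varies with need, so some participants may start earlier.

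**Conclusion.** The concern holds as one of attribution. The trial estimates SBIRT plus CAP versus usual care for screening, DIS and LS7. The component effects named in Aims 1–3 are not identifiable, and the protocol's own citation on motivational interviewing makes the CAP attribution for DIS and LS7 unsupported. The size of any misattribution cannot be stated, because the data cannot divide θ between *s* and *c*. The validity of the arm comparison, the 22 churches and the 440 subjects are unaffected.

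The 3-month FFQ conflict is secondary. The protocol mentions those data only for sensitivity analyses and does not say how they enter, so the finding is that the two descriptions must be reconciled, not that a particular analysis is wrong. Calling the 3-month difference mainly pre-CAP assumes the described sequence is followed. A comparison between arms at 3 months also assumes that usual care completes that FFQ. The Outcomes section sets no restriction by arm, but the Trial Design wording ties the collection to CAP.

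**What to change.** 1. Restate Aims 1–3, their hypotheses and the power and analysis text as the effect of the combined SBIRT and CAP programme versus usual care. Relabel the model indicator (1 = SBIRT plus CAP). This matches the abstract, the comparator section and Sequence Generation. Make no causal claim for either component on its own.
2. Give the 3-month FFQ one role throughout: a post-randomisation measure, not a baseline covariate. State that it is collected in both arms, if that is the intention.
3. Report the 3-month and 6-month DIS differences between arms separately. Label the 3-month difference as supportive, mainly pre-CAP evidence, and note that CAP start may vary by participant.

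The cost is protocol wording and one additional reported contrast from data already planned, with no redesign or recalculation. The downside is narrower claims about the individual components.
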